### The PRIDE Survey

The final PRIDE survey comprised three main sections as follows (Figure 1): (1) participant screening; (2) demographics; and (3) 39 test items, together with the LGBT-DOCSS [22] and 12 items from the LGBTCI scale [24]. The questionnaire items were translated and back translated for the Italian version. A copy of the final English version of the questionnaire is available as Multimedia Appendix 1. The protocol was developed and completed using the SPIROS (Standardized Protocol Items Recommendations for Observational Studies) guidelines (Checklist 1) [34].

**Figure 1. F1:**
[figure not shown]
Flow diagram of the Professional Readiness in Diversity and Equity (PRIDE) questionnaire structure. LGBT-DOCSS: Lesbian, Gay, Bisexual, and Transgender Development of Clinical Skills Scale; LGBTCI: LGBT Climate Inventory.

### Study Procedure and Recruitment

#### Recruitment, Enrollment, and Consent

A convenience sampling approach was adopted and complemented by snowball recruitment. The survey link(s) and/or QR code was distributed via professional mailing lists, LGBTQI+ associations, and international conferences with recipients encouraged to forward it to colleagues to maximize dissemination for recruitment purposes. Additional routes included undergraduate and postgraduate teaching sessions providing recruitment opportunities for both the United States and European sites. Boston University (United States) used individualized links for medical school faculty, with other centers using an anonymous link (a common link for all participants from the same institution was created, and this link was different for each institution participating in the study).

The introductory page of the survey included detailed participation information and details of relevant support organizations for issues covered by the survey. Information was provided about the project, including details of what participants were required to do and how long it would take to complete the questions. A statement was provided regarding data protection, including confidentiality and anonymity. Potential participants were asked to click on a box to confirm that they had met the following criteria: (1) read and understood the participant information before proceeding, (2) understood that the survey was voluntary and that they agreed to participate, and (3) they were 18 years of age or older. There were minor variations in how this information was presented and/or its level of detail between European and US sites to allow for cultural variations and accepted practices within the guidance of the relevant institutional review boards (IRBs).

#### Data Management

The data collection was carried out using a General Data Protection Regulation (GDPR) [35] compliant platform. The REDCap (Vanderbilt University) platform [36,37] was hosted on secure institutional servers, ensuring compliance with the EU GDPR 2016‐679, United Kingdom Data Protection Act 2018 [38], and the US Common Rule Department of Health and Human Services 45 CFR 46 [39]. For the United Kingdom, REDCap v.16.0.15 was used; for the United States and Italy, REDCap v.16.1.6 was used.

Data were entered directly by participants through REDCap, thereby excluding data entry errors and transcription risks. All fields that formed part of the PRIDE scale (39 items) were set as required (to minimize incomplete data). Each record was automatically time-stamped with the date and time of completion. No personally identifiable information was stored alongside survey responses. Access to identifying information (eg, participant contact list) is restricted to authorized personnel and stored in a separate, secure REDCap instrument, linked only through coded identifiers.

Data quality checks were performed using REDCap’s Data Quality module and ad hoc statistical syntax scripts. Data will be exported in deidentified format to statistical software (Stata v.17) for psychometric and statistical analyses. Data export rights are restricted to authorized personnel. Variable names, labels, and coding schemes will follow the project’s codebook, ensuring reproducibility and interoperability across analysis phases.

### Statistical Analysis

#### Analytical Methods

All analyses will be performed using Stata (v.17) and R (v.4.5.1; R Foundation for Statistical Computing); Figure 2 shows the planned statistical analysis flowchart. We begin by analyzing the distributions of scale items. Continuous variables will be analyzed using descriptive statistics such as mean, median, standard deviation, quartiles, and IQRs, while for categorical variables, frequencies, proportions, or percentages will be used. Given the probable nonnormal distribution of items and scale scores, numerical comparisons will be performed using Dunn [40] test for stochastic dominance among multiple pairwise comparisons, following a Kruskal-Wallis test of stochastic dominance among k groups [41]. We will use EFA and CFA to identify dependence structures among measures, and item response theory (IRT) to explore factor diagnostics and retain items that carry the greatest exploratory power. Validation analyses will be conducted using the Kruskal-Wallis test with Bonferroni correction for multiple comparisons.

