In designing the scale, the team made several decisions to ensure applicability and interpretability. We drew upon existing implicit bias scales. While the scale is aimed toward those who provide clinical care, we ensured that the questions had a broad reach by using “clients or patients” instead of “patients” alone. We also avoided questions that were overly technical or related to specific specializations. While we believe it is important to address the needs of specific sexual and gender minority groups, we restricted these to a few questions rather than repeating questions by group. We elected to phrase questions in a way that addresses perceptions of one’s specific institution rather than perception of self. Finally, we avoided some questions over concerns about long-term relevance (eg, specifying pronouns when working with colleagues or clients, as this may become more normalized over time).

In addition to the 100 test items, to enable convergent construct validity testing and criterion and concurrent validity testing of the PRIDE scale, 2 further scales were used forming part of the main survey; these included the LGBT-DOCSS [22]; and the LGBTCI [24,28]. The LGBT-DOCSS is an internationally established, interdisciplinary self-assessment for health and mental health professionals working with LGBT clients [21]. The scale is comprised of 18-items and 3 subscales (clinical preparedness, attitudes, and knowledge). Items are rated on a 7-point Likert scale (1 strongly disagree to 7 strongly agree), with 8 items reverse-scored. For our purposes, we adjusted this to a 5-point scale, as we felt it would reduce cognitive load and potentially improve response rates. The loss of granularity would have minimal to no loss of psychometric information. From these items, a total mean score and 3 subscale scores (clinical preparedness, attitudes, and knowledge) can be computed. Higher scores thus reflect greater levels of LGBT cultural competence. The LGBT-DOCSS has demonstrated strong reliability and construct validity [22]. The LGBTCI is a well-used and researched assessment of LGBT workplace support and overall climate [24,28]. For this survey, we used only the 12-item Workplace Support subscale, in which items are rated on a 4-point Likert scale from 1 (doesn’t describe at all) to 4 (describes extremely well).

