**Figure 2. F2:**
[figure not shown]
Professional Readiness in Diversity and Equity (PRIDE) scale statistical analysis plan for scale evaluation. CFI: comparative fit index; GRM: graded response model; ML: maximum likelihood; RMSEA: root mean square error of approximation; SRMR: standardized root mean square residual; TIFs: test information functions; TLI: Tucker-Lewis index.

Missing data will be assessed prior to all analyses. For the United States sample, participants were required to fill all survey items, with branching (skip) logic implemented for respondents who did not currently engage in clinical practice. For the European sample, participants were permitted to skip responses for demographics only. We concatenated all complete and partial responses and participants with more than 10% of items missing will be excluded. For the remaining participants, missing values in the CFA framework will be handled using full information maximum likelihood estimation [42,43]. Descriptive and known-groups validity analyses will use pairwise deletion. The proportion and pattern of missing data will be reported, and missing completely at random test by Little will be used to evaluate the missing data mechanism.

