Finally, the PRIDE Scale captures health care professional–reported competence and perceived workplace climate but does not incorporate patient-reported experiences or objective behavioral indicators of inclusive care. Triangulation with patient outcomes, simulated clinical encounters, or organizational audit data will be necessary in future work to fully establish the criterion validity and real-world utility of the instrument. Future longitudinal work will be required to establish these properties and to assess the scale’s responsiveness to educational or organizational interventions.

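### The only test named for the validation analyses is Kruskal-Wallis, which compares groups and cannot measure how strongly PRIDE scores agree with the LGBT-DOCSS and LGBTCI scores

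*Protocol article*

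**What the plan says.** Under Scale Development and Measures, the protocol article explains that the LGBT-DOCSS and the LGBTCI were included "to enable convergent construct validity testing and criterion and concurrent validity testing of the PRIDE scale". Both are scored numerically. For the LGBT-DOCSS, "a total mean score and 3 subscale scores (clinical preparedness, attitudes, and knowledge) can be computed". For the LGBTCI, "we used only the 12-item Workplace Support subscale", with each item rated 1 to 4.

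Under Statistical Analysis, Analytical Methods, the plan first describes numerical comparisons by Dunn's test "following a Kruskal-Wallis test of stochastic dominance among k groups". It closes the paragraph with "Validation analyses will be conducted using the Kruskal-Wallis test with Bonferroni correction for multiple comparisons". The missing-data paragraph that follows mentions one specific kind of validity analysis: "Descriptive and known-groups validity analyses will use pairwise deletion".

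The later analysis sections cover factor analysis, measurement invariance, item response models and reliability, all for PRIDE's own items and scores. The one correlation of PRIDE scores that is named is the two-week test-retest correlation.

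**The concern.** Convergent and concurrent validity ask how closely the new score tracks an existing one, and whether it tracks the matching construct better than a different one. The answer is a coefficient with its uncertainty. Kruskal-Wallis asks whether at least one of several groups tends to score higher than another. To use it on two numeric scores, one of them must first be turned into groups, and the output is then a test statistic and a p-value.

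The article gives validation to this test in general terms, so the comparison with the LGBT-DOCSS and LGBTCI has either an unsuitable method or none. Part of the case for PRIDE as a valid instrument rests on that comparison. If it were reported as significance alone from more than a thousand respondents, readers could not tell a scale that agrees well with its comparators from one that barely does.

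**Working it through.** The plan states no power or effect size for the validation analyses, so there is no figure to reproduce. The check has two parts.

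**1. Purpose against method**

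| Question | What the article provides |
|---|---|
| Agreement with LGBT-DOCSS total and three subscales (numeric) | No coefficient named; only the general Kruskal-Wallis sentence |
| Agreement with LGBTCI Workplace Support (numeric) | The same |
| Matching versus non-matching subscales | Nothing named |
| Differences between known groups | Kruskal-Wallis, which suits this use |
| Stability over two weeks | A correlation is named |

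**2. What a significant Kruskal-Wallis result would show**

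Inputs from the article: 1339 eligible completers (Abstract and Results), and a 50/50 split within country, so about 670 per half. Assumptions, because the article does not give them for these tests: overall alpha 0.05, the comparator cut into three equal groups, 1 to 20 Bonferroni tests, and bivariate normal scores. Twenty tests would be five PRIDE domains by four comparator scores (three LGBT-DOCSS subscales and one LGBTCI subscale).

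*Smallest significant effect.* Epsilon-squared, the share of rank variance explained, equals the chi-square critical value on 2 degrees of freedom divided by (n − 1).
- n = 1339, 1 test: 5.991 / 1338 = 0.0045
- n = 1339, 20 tests (alpha 0.0025): 11.983 / 1338 = 0.0090
- n = 670, 1 test: 5.991 / 669 = 0.0090
- n = 670, 20 tests: 11.983 / 669 = 0.0179

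With all respondents, less than 1% of rank variance is enough even after 20-fold correction.

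*Probability of significance.* Simulation with 4,000 replicates: draw pairs with correlation r, cut the comparator at its tertiles, and apply Kruskal-Wallis to the other score.

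| n | r | 1 test | 4 tests | 10 tests | 20 tests |
|---|---|---|---|---|---|
| 1339 | 0.05 | 26% | 12% | 7% | 5% |
| 1339 | 0.10 | 82% | 65% | 53% | 45% |
| 1339 | 0.15 | 99% | 98% | 95% | 93% |
| 1339 | 0.50 | 100% | 100% | 100% | 100% |
| 670 | 0.10 | 51% | 30% | 20% | 15% |
| 670 | 0.15 | 87% | 72% | 61% | 52% |
| 670 | 0.50 | 100% | 100% | 100% | 100% |

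Separate runs differ by about a percentage point. Across runs, r = 0.15 gives 92–100% at n = 1339 and 52–88% at n = 670. Quartiles instead of tertiles change little: at n = 1339, r = 0.15 gives 99% with one test and 95% with ten.

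A correlation of 0.15 corresponds to 0.15² = 0.0225, about 2% shared variance. With all respondents it is nearly as likely to be significant as a correlation of 0.50.

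*What a coefficient would show.* The 95% interval on the Fisher scale is atanh(r) ± 1.96 / √(n − 3). At n = 1339 the half-width is 1.96 / √1336 = 0.0536.
- r = 0.15: 0.1511 ± 0.0536, back-transformed 0.10 to 0.20
- r = 0.50: 0.5493 ± 0.0536, back-transformed 0.46 to 0.54

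The two intervals are far apart. This formula is for a Pearson correlation; a Spearman interval would be slightly wider.

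**The case against.** The best reply is that the Kruskal-Wallis sentence was meant for known-groups validity. The same paragraph describes the test as a comparison of groups, known-groups analyses are named shortly afterwards, and the test suits them. This is a condensed article, Figure 2 is not shown, and convergent correlations may stand in a fuller plan. That reading is plausible, but the sentence does not state it. It covers the validation analyses as a whole, in an article that elsewhere promises convergent, criterion and concurrent testing. Even on the kinder reading the sentence has to be limited. The point concerns a method that is stated and does not fit, not a detail left out.

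Four stronger readings are tempting, and the document does not support them.
- *The comparators will be cut into categories.* Nothing says so. The tertiles above only illustrate what applying the test to these scores would entail.
- *The validation cannot fail.* That goes too far. The sentence includes a Bonferroni correction, and at r = 0.10 the chance of significance at n = 1339 falls from 82% with one test to 53% with ten. At r = 0.05 it is low throughout.
- *P-values will be reported without effect sizes.* The article is silent on this, and silence is not a statement. Any significance test, including one on a Spearman coefficient, would also flag small correlations at this sample size. The argument is for reporting the size of the association.
- *The word criterion must go.* This is a labelling preference. The Limitations section already says that patient outcomes, simulated encounters or audit data are needed "to fully establish the criterion validity and real-world utility of the instrument".

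**Conclusion.** The point holds in this form. The article collects two numeric comparator scales for validity testing, but the only method it states for validation compares groups and gives no strength of agreement. If that test were used on categorised comparator scores, a correlation near 0.15 would be called significant in about 92–100% of cases with all 1339 respondents, and in about 52–88% with one half. Significance would then say little about whether convergence is weak or good.

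These figures rest on assumed tertiles, alpha 0.05, 1 to 20 tests and normal scores. The usable number may also fall below 1339 once respondents with more than 10% of items missing are excluded. The mismatch between purpose and method does not depend on any of these assumptions. The plan should be corrected before the comparator results are examined. Kruskal-Wallis remains suitable for known groups.

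**What to change.** 1. Limit the Kruskal-Wallis sentence in Analytical Methods to known-groups comparisons, and report each with an effect size and confidence interval.
2. For the comparator scales, state Spearman correlations, or latent correlations from a joint factor model, with 95% confidence intervals. Give them for each PRIDE subscale with each LGBT-DOCSS subscale and with LGBTCI Workplace Support.
3. Fix the expected pattern before the comparator results are seen: matching subscales should correlate more highly than non-matching ones. Any threshold should be set and justified by the sponsor, since the article offers no basis for a particular value.

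The cost is a revised sentence, a correlation table and a small amount of extra analysis, with no new data. Timing matters. Data collection is complete, and the article's own statements on analysis differ: the Abstract says it has started, while the Results section places it in Summer 2026. The amendment should therefore be dated and should say whether any comparator results had been seen.

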### Study Population and Sample

The study population consisted of health professionals, including students or health professionals-in-training, such as physicians, nurses, and other allied health professionals (eg, podiatrists, occupational therapists, physiotherapists, and mental health professionals) working in Italy, the United Kingdom, and the United States, with respondents able to complete the survey in English or Italian, depending on the country. The goal was to have a norming sample of international health care professionals including those in-training.

Sample size was calculated considering the 2 main statistical techniques to be used in the analysis: exploratory factor analysis (EFA) and confirmatory factor analysis (CFA). Based on the literature, as a rule of thumb (item-to-participant ratio), 5 to 10 participants per item are required [29-32]. For the 39-item PRIDE scale, this would translate to a minimum of 195 participants (5 participants per item) and a preferred sample size of 390 participants (10 participants per item). However, as we are planning an EFA and CFA, a total of approximately 700 participants is planned. For test-retest reliability, based on Walter et al [33], and assuming a null intraclass correlation coefficient of 0.40, an expected intraclass correlation coefficient of 0.70, 2 administrations of the scale, a significance level (α) of 0.05, and a power (1–β) of 0.80, a sample size of 62 is required.

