#### EFA and CFA

EFA will be conducted to examine the underlying dimensional structure of the PRIDE scale and to inform item retention. As an initial parametric approach, EFA will be performed using principal component analysis (PCA) with varimax (orthogonal) rotation to obtain a simple and interpretable factor solution. Prior to extraction, the suitability of the data for factor analysis will be assessed (eg, inspection of the correlation matrix and standard measures of sampling adequacy). The number of factors to retain will be determined using the Kaiser criterion (eigenvalues ≥1) in conjunction with visual inspection of the scree plot to identify the point of inflection. Items will be evaluated based on their pattern of loadings, and only items with primary factor loadings ≥0.40 will be considered for inclusion. Items showing substantial cross-loadings (eg, ≥0.30 on more than 1 factor) or weak or unstable loadings will be reviewed for removal or revision, with decisions guided by both statistical evidence and conceptual coherence with the intended constructs. Given the ordinal nature of Likert-type responses, a complementary nonparametric ordinal approach will also be implemented. Specifically, a polychoric correlation matrix will be estimated and subjected to factor analysis with varimax rotation, applying the same factor-retention rules (eigenvalues ≥1 and scree plot) and item-selection criteria (primary loading ≥0.40, limited cross-loading). Consistency of the factor structure across the PCA-based and polychoric-based solutions will be examined to strengthen inferences regarding dimensionality and to ensure that the final factor model is robust to distributional assumptions. We acknowledge that PCA is technically a data-reduction technique that accounts for total item variance rather than modeling shared latent variance exclusively, and therefore does not constitute a latent variable model in the strict sense [30,44]. Its use here is pragmatic, consistent with its established role as an initial item-selection tool at the exploratory stage. The robustness of the dimensional solution will be evaluated formally through the planned cross-validation against the polychoric-based factor solution and, most importantly, through the subsequent CFA with maximum likelihood estimation, which will constitute the primary evidence for the latent structure of the PRIDE Scale.

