## Results

Data collection funded in May 2023 and was conducted from October 2024 to December 2025, with a total of 1339 eligible participants who completed the survey. Data cleaning and preparation are underway, and data analysis will take place in Summer 2026, with the first results paper expected to be submitted in Autumn 2026.

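### Plain Bonferroni is prespecified for the validation comparisons; Holm gives the same family-wise error control and is never less powerful, a free but modest improvement

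*Protocol article*

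**What the plan says.** The statement is in the protocol article, Analytical Methods. Scores are expected to be non-normal, so "numerical comparisons will be performed using Dunn [40] test for stochastic dominance among multiple pairwise comparisons, following a Kruskal-Wallis test". The paragraph ends: "Validation analyses will be conducted using the Kruskal-Wallis test with Bonferroni correction for multiple comparisons". The paragraphs on missing data that follow name known-groups validity among the planned analyses.

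The article gives no number of groups, number of comparisons, effect size or power target for these tests. Study Population and Sample bases the sample size on item-to-participant ratios ("as we are planning an EFA and CFA, a total of approximately 700 participants is planned") and on a separate test-retest calculation. Results reports the sample obtained: "with a total of 1339 eligible participants who completed the survey".

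**The concern.** Known-groups validity is shown by finding score differences between groups that are expected to differ. With three or more groups, the evidence is strongest when the individual pairs can be separated. Bonferroni holds every pair to the strictest threshold, even after other pairs have been declared different. Holm relaxes the threshold after each rejection and keeps the same family-wise guarantee.

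Choosing between the two for p-value decisions is therefore not a trade of error control against power. What is at stake is some avoidable loss of power to separate pairs of groups when the true differences are small. The validity of the tests is not in question.

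**Working it through.** **Inputs.** From the article: Kruskal-Wallis, Dunn, Bonferroni (Analytical Methods) and 1339 respondents (Results). Assumed, because the article does not give them: two-sided family-wise α of 0.05 (the article states 0.05 only for the test-retest calculation), three groups and so m = 3 pairs, normal scores with SD 1, and the group sizes and shifts below. The article gives no power figure for these tests, so there is none to reproduce.

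**Step 1: Bonferroni is valid.** Each of m tests is run at 0.05/m. Under independence the family-wise error is 1 − (1 − 0.05/m)^m, which gives 0.0492 for m = 3, 0.0490 for m = 6 and 0.0489 for m = 10. All are within 0.05.

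**Step 2: why Holm dominates.** Order the p-values. For m = 3 Holm compares the smallest with 0.05/3 = 0.0167, the next with 0.05/2 = 0.025 and the last with 0.05, stopping at the first failure. Bonferroni compares all three with 0.0167.
- Holm's thresholds are never lower, so it rejects everything that Bonferroni rejects.
- The first threshold is the same, so the chance of at least one rejection is the same.
- With m = 1 the methods coincide.

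**Step 3: size for one pair.** Approximate power for a standardised difference d with n per group is Φ(d/√(2/n) − z). For n = 446 and d = 0.2, d/√(2/n) = 2.987.
- At 0.0167 (z = 2.394): Φ(0.593) = 0.723.
- At 0.05 (z = 1.960), Holm's most lenient step: Φ(1.027) = 0.848.

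Holm's gain for this pair lies between zero and that gap, depending on how many other pairs are rejected first.

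**Step 4: the planned sequence simulated.** Kruskal-Wallis at 0.05, then Dunn tests, about 1339 respondents in three equal groups. Average power per true pairwise difference:

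| Pattern of group means | Bonferroni | Holm | Gain (points) |
|---|---|---|---|
| Even steps of 0.15 SD | 0.61 | 0.68 | 7 |
| Even steps of 0.20 SD | 0.796 | 0.879 | 8.3 |
| One group shifted 0.2 SD | 0.705 | 0.739 | 3.4 |
| Even steps of 0.30 SD | 0.983 | 0.993 | 1.0 |
| One group shifted 0.3 SD | 0.977 | 0.984 | 0.7 |
| Even steps of 0.50 SD | 1.00 | 1.00 | 0 |

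- No simulated data set had a pair rejected by Bonferroni but not by Holm.
- The chance of at least one true detection was identical (0.848 for both with one group shifted 0.2 SD).
- The chance of detecting every true difference at steps of 0.20 SD rose from 0.426 to 0.657.
- With all groups equal, family-wise error was 0.044 for both.
- With one group shifted 0.2 SD, the error on the remaining null pair was 0.013 for Bonferroni and 0.030 for Holm. Holm uses more of the 5% allowance but stays inside it.

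**Step 5: sensitivity.**
- Uneven split of 1339 (800/270/269): 0.697 to 0.786 for steps of 0.20 SD, 0.930 to 0.968 for steps of 0.30 SD, and 0.536 to 0.567 for one group shifted 0.2 SD.
- The planned 700 in equal groups: gains of about 3 to 7 points at 0.2 to 0.3 SD and essentially none at 0.5 SD.

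**The case against.** The strongest reply is that nothing here is wrong. Bonferroni is valid, prespecified and simple, and no stated sample size, power figure or conclusion depends on it. That stands, and it is why this is offered as an improvement and not as an error.

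A reader might go further and infer that the study will miss real group differences for nothing. The article does not support that. It gives no effect size, number of comparisons or power target from which such a loss could be shown. In balanced groups the gain almost vanishes from about 0.3 SD upwards. The largest gains come from patterns in which every pair truly differs, because each rejection then relaxes the next threshold.

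Three further points stand in part.
- The family is not defined. The sentence on Dunn's test names no correction, and Bonferroni could apply to the pairs, to several Kruskal-Wallis tests, or to both. The size of the gain therefore cannot be fixed, though Holm is at least as powerful in any family.
- Bonferroni gives simple simultaneous confidence intervals, but the article plans none for these comparisons.
- Known-groups comparison is one strand of validation. EFA and CFA makes the CFA the analysis "which will constitute the primary evidence for the latent structure of the PRIDE Scale", and the correction does not touch it.

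**Conclusion.** The point holds as an optional refinement of minor importance. Holm keeps the family-wise guarantee under any dependence and cannot lose power against Bonferroni; that conclusion needs no assumption about group sizes or effects. The size of the benefit does. With three equal groups drawn from 1339 it is 7 to 9 points of average power for small, evenly spaced differences, 1 to 3 points in the milder patterns, and nil for large effects. The stronger reading, that true differences will be lost, is not established.

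**What to change.** In Analytical Methods, replace 'Bonferroni correction' with 'Holm (step-down Bonferroni) correction', applied to the same family of comparisons.

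The cost is a few words in the plan and a change of adjustment method in the analysis code, with no change to data or sample size. The one condition is timing. The Abstract says analysis has started, while Results places it in Summer 2026. The change should be dated and documented before the validation comparisons are run. If their results have already been seen, a move to the more permissive procedure should be disclosed as post hoc, with the Bonferroni results reported alongside.
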